#### Validation of self-report by saliva cotinine samples

Several studies have demonstrated the utility of collecting saliva cotinine samples by mail using the same Salivette sampling method proposed for this study [14,15]. While clinically tobacco exposure is measured by quantifying cotinine in either plasma or urine, salivary cotinine is a reliable measure of nicotine or tobacco exposure that is widely used in both clinical and epidemiological or population-based studies [23-25]. Participants will be asked to collect their saliva sample at baseline and on the day they complete their follow-up interviews (saliva collection kits mailed several days following baseline interview and one week before each follow-up interview is due, along with a reminder letter about the upcoming telephone interview). At baseline, the saliva sample will allow for the calculation of the 3-HC/cotinine ratio to test the moderating hypothesis of nicotine metabolism rate on success at tobacco cessation using nicotine patches. Collection of saliva samples at follow-up periods will allow for the verification of smoking abstinence.

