#### Criteria for Assignment to the Randomized Controlled Trial

As part of the baseline survey, all subjects will be asked a series of questions to assess their level of interest in receiving free NRT: "The Ministry of Health is considering different ways to help people stop smoking. One option would be to provide interested smokers with free Nicotine Patches. If Nicotine Patches were offered for free, would you be interested in receiving them?" Those who say "yes" will then be asked if they would use the nicotine patch to quit smoking. Those who say "yes" to this question will be asked if they would begin to use the patch within 1 week of receiving it. A "yes" to this question will lead to being asked if they would be willing to have the Patch sent to their home. These questions have been used in a previous survey and form the basis of the sample size estimate for the present study [10]. Finally, as part of the demographic section of the survey, subjects will also be asked questions regarding health conditions contraindicating NRT use (i.e., being pregnant, intending to become pregnant, or breastfeeding; having a serious heart or circulation problem, not including high blood pressure). Subjects will be eligible for the randomized controlled trial if they are interested in NRT, would use it to quit within 1 week of receipt, are willing to have the NRT sent to their home, and have no health contraindications for the use of NRT. Subjects who meet all these eligibility criteria will then be randomly assigned to the experimental or control condition.

Although some participants will report that they have used NRT in the past, they will not be excluded from the study due to prior NRT use because the intent is to evaluate the impact of NRT in the full range of potential community participants. In addition, our previous research has indicated that prior use of NRT is actually positively related to current interest in using NRT again [10]. Thus, one of the secondary analyses of this study will test the moderating hypothesis that prior use of NRT is negatively related to future success with NRT when it is offered for free.

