### Interventions

#### Experimental condition

A randomized half of the subjects meeting baseline criteria and expressing an interest in receiving free nicotine patches, willingness to use the Patches within a week to quit smoking, interest in having the patches sent to their home, and meeting criteria for eligibility to receive NRT (i.e., no health contraindications) will be randomly assigned to the experimental condition (the remainder will be assigned to the control condition). Subjects in the experimental condition will be asked, at the end of the baseline survey, if they want to be sent a free, 5-week supply of Nicotine Patches. Those who say "yes" will have the NRT mailed to their home the week after their baseline interview. As is employed in the Ontario mass distribution of NRT initiative [12], a 5-week program of nicotine patches will be sent (3 weeks of Step 1 [21 mg of nicotine]; 1 week of Step 2 [14 mg of nicotine]; 1 week of Step 3 [7 mg of nicotine]). Once randomly assigned to this condition, subjects will be counted as part of the experimental condition whether they agree to accept the NRT or not (intent-to-treat approach).

The 5-week program of nicotine patches was chosen for pragmatic reasons, which balanced a limited budget to supply the NRT and conduct a large population survey, and because of findings from literature regarding effective treatment duration. A recent Cochrane review evaluating the efficacy of NRT has revealed no differences in treatment effect between trials offering up to eight weeks of nicotine patch treatment and those offering longer treatments [16]. Furthermore, several trials evaluating usage patterns of free nicotine patches offered to smokers through a Smokers' Quitline have shown no differences in 7- and 12-month quit rates between individuals receiving 2, 4, 6, or 8-week supplies of free nicotine patches [17,18]. These findings however, are inconsistent with two other studies demonstrating higher quit rates among Smokers' Quitline callers receiving 8 weeks versus 2 weeks of free nicotine patches [19], and 6 weeks versus 4 weeks of free NRT [20]. Given the apparent inconsistencies in the literature surrounding effective treatment duration of mailed out free NRT, we chose a middle of the road approach of 5 week nicotine patch program.

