### Randomization

Recruitment is conducted using a Random Digit Dialing survey with computer assisted telephone interview (CATI) technology. At the end of the baseline interview, eligible subjects will be allocated to experimental and control conditions using a simple randomization without replacement built into the CATI program (no stratification or minimization given the large proposed sample size in this trial).

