Subgroup analyses will examine quit rates among subjects within the experimental and control conditions who: (a) are slow versus fast nicotine metabolizers as measured by the 3-HC/cotinine ratio; (b) report using all 5 weeks of the free NRT they were sent as compared with those who do not use all 5 weeks; (c) had used NRT for a quit attempt at least once before participation in the proposed study as compared with those who had never used NRT before; and (d) are male or female (to assess any interaction by sex). Further, we will compare subjects in the experimental condition who used the NRT to just those subjects in the control condition who did not use any NRT during the same time period (i.e., they did not obtain NRT from other sources). Finally, using just the baseline data (N = 1,000), we will relate the 3-HC/cotinine ratio to patterns of smoking and prior use of NRT.

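### The 'baseline' saliva sample for the 3-HC/cotinine moderator is collected after randomisation and after the patch offer, so its timing and return may differ by arm

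*Protocol article*

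**What the plan says.** Four statements in the protocol article fix the order of events.

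- Randomization: "At the end of the baseline interview, eligible subjects will be allocated to experimental and control conditions".
- Experimental condition: "Subjects in the experimental condition will be asked, at the end of the baseline survey, if they want to be sent a free" supply of patches. Those who accept "will have the NRT mailed to their home the week after their baseline interview".
- Validation of self-report by saliva cotinine samples: "saliva collection kits mailed several days following baseline interview and one week before each follow-up interview is due". The same section calls this sample a baseline one and uses it "to test the moderating hypothesis of nicotine metabolism rate on success at tobacco cessation using nicotine patches".
- Criteria for Assignment to the Randomized Controlled Trial: to be eligible, subjects must have answered yes when asked "if they would begin to use the patch within 1 week of receiving it".

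The Analysis Plan enters the ratio as a main effect in Step two of the logistic regressions and as an interaction with condition in Step three, and lists slow versus fast metabolisers as a subgroup. It also states that "using just the baseline data (N = 1,000), we will relate the 3-HC/cotinine ratio to patterns of smoking and prior use of NRT". The Power analysis section says that baseline saliva is taken only from the 1,000 subjects in the randomised trial.

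**The concern.** A moderator should be measured before allocation, or at least be something that allocation cannot touch. Here the kit leaves after one arm has been offered a product and the other has been offered nothing. Two consequences follow.

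**Measurement.** An experimental subject who delays the sample may give it while wearing a patch or after cutting down or stopping. A control may do the same, but is less likely to. The ratio could then be measured under conditions that differ on average by arm. The planned description of the ratio against smoking pattern also presumes that the subject was still smoking as usual when sampled.

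**Selection.** A ratio exists only for those who return a kit, and return comes after randomisation. If it depends on arm and on motivation to quit, the arms are no longer a randomised comparison among returners. This holds even if patch use leaves the ratio itself unchanged.

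At stake is the metabolism question, which Aim of the study names as something the trial will explore. A mistimed sample cannot be retaken.

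**Working it through.** **1. The plan's own figure.** The article gives no sample size for the moderator analysis, so the figure to reproduce is the 403 per condition in Power analysis. Inputs: 3.7% and 8.7%, alpha 0.05 (taken as two-sided), power 80%, continuity correction.

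- Uncorrected: n = [1.960·√(2·0.062·0.938) + 0.842·√(0.037·0.963 + 0.087·0.913)]² / 0.05² = 364.
- Corrected: n' = (364/4)·[1 + √(1 + 4/(364·0.05))]² = 403.
- With 20% attrition: 800/0.8 = 1,000.

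Both figures reproduce. Neither depends on the baseline saliva.

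**2. Order of events.** Allocation and offer (end of call), then kit posted (several days later), then patches posted (the week after), then patch use (intended within a week of receipt). Nothing in the article asks for saliva before patch use or a change in smoking, and nothing ties patch mailing to return of the kit. The sample is after randomisation on any reading.

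**3. How close the two parcels are.** Calendar days are not given. Assume the kit is posted on day 3–5, the patches on day 7–14, and post takes 2–5 days.

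- Kit arrives: 3 + 2 to 5 + 5 = day 5–10.
- Patches arrive: 7 + 2 to 14 + 5 = day 9–19.

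Arrivals overlap only on days 9–10. With equal postage the kit leads by 7 − 5 = 2 to 14 − 3 = 11 days. A sample taken promptly usually precedes the patches; one delayed by a few days to two weeks may not.

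**4. Selection by return (return rates assumed; quit rates from Power analysis).** Among returners in the experimental arm, quit rate = q·a / [q·a + (1 − q)·b], where a and b are the return rates of later quitters and non-quitters.

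| q | a, b | Quit rate among returners |
|---|---|---|
| 8.7% | 80%, 80% | 8.7% |
| 8.7% | 90%, 70% | 0.0783/0.7174 = 10.9% |
| 8.7% | 90%, 50% | 0.0783/0.5348 = 14.6% |
| 3.7% (no true effect) | 90%, 70% | 0.0333/0.7074 = 4.7% |
| 3.7% (no true effect) | 90%, 50% | 0.0333/0.5148 = 6.5% |

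On the odds scale, return multiplies the odds of quitting in that arm by a/b. If a/b differs by arm, the arm contrast among returners is biased. If a/b is the same for slow and fast metabolisers, it cancels from the logistic interaction term. The interaction is distorted by selection only if return also varies with metabolism.

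**5. Number of samples.** Assume a median split on the ratio, 3.7% quitting in both control groups, and experimental rates of 11.2% and 6.2% (differences of 7.5 and 2.5 points, an interaction of 5 points). With return rate r, each of the four cells has 500r/2 subjects, and power ≈ Φ(0.05/√V − 1.96), where V = (2·0.037·0.963 + 0.112·0.888 + 0.062·0.938)/(250r).

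- r = 100%: 38%
- r = 80%: 31%
- r = 60%: 25%

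The 97% in Criteria for Participation in baseline survey is the usable share of samples collected by mail, not a return rate.

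**The case against.** The strongest reply is that the sequence is real but its consequences are assumed. Most of this stands.

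- A reader might infer that only experimental subjects can sample on a patch or after stopping. The documents do not support that. The follow-up interviews ask controls about NRT bought elsewhere, the Analysis Plan separates controls who used none, and Power analysis expects 3.7% of controls to have quit at 6 months. The difference is one of likelihood.
- A reader might infer that the ratio is contaminated. Nothing in the article says how far patch use or a few days' abstinence changes it, and it is used as a marker of metabolism, not of amount smoked. This is a risk, not a demonstrated error.
- Differential return is not shown. Willingness to give saliva is an entry criterion, Design offers a $20 honorarium for baseline and each follow-up, and controls are not led to expect patches. These points lessen differential return without excluding it.
- The 1,000 can be read as the planned baseline set, since only trial subjects give saliva, rather than as a forecast that every kit comes back.
- A condensed article may leave kit instructions and date fields to the full protocol. That is fair for those details, but the mailing schedule itself is stated here, and it puts the sample after the offer.

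The obvious remedy, keeping only samples dated before first patch use, would also do harm. It removes early starters from the experimental arm with no matching exclusion in controls. It also relies on recall at 8 weeks of how soon after receipt use began, which is missing for those lost by then.

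**Conclusion.** The point holds in limited form. On the stated schedule, the sample called baseline is taken after randomisation and after the patch offer, and the subjects who have a ratio are selected by a later return that may differ by arm. That much follows from the text without assumptions.

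The size is not shown. The arrival windows, the return rates and the power figures above rest on assumed inputs and serve only for scale; if return is unrelated to quitting, the selection shift is nil.

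It would be wrong to conclude that the main result is threatened. Step one compares quit rates by assigned condition and does not use the baseline saliva, and the 403 per condition stands. Only the metaboliser interaction, the metaboliser subgroup and the description of the ratio against smoking pattern and prior NRT use are affected. The change is still worth making before recruitment, because it is cheap and the sample cannot be recovered later.

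**What to change.** 1. Mail the saliva kit the day after the interview, with an instruction to collect on receipt, and leave the patch mailing unchanged. Under the postage assumed above, the kit would arrive on day 3–6 (1 + 2 to 1 + 5), before the earliest patch arrival on day 9.
2. Have the subject record the collection date.
3. In the moderator and baseline-ratio analyses, keep samples collected within one days-since-interview limit that is identical in both arms and set before the earliest possible patch arrival under the actual mailing calendar. Do not base the exclusion on first patch use.
4. Report kit return by arm.
5. Describe the ratio as measured shortly after randomisation, and state the number of valid samples in place of 1,000.

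The cost is an earlier mailing date, one date field and the loss of some late samples from a secondary analysis. If patches can go out sooner than assumed here, the limit falls earlier and more samples are lost. Selection by return is reduced and made visible, but not removed, because the kit still follows the offer.

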### Randomization

Recruitment is conducted using a Random Digit Dialing survey with computer assisted telephone interview (CATI) technology. At the end of the baseline interview, eligible subjects will be allocated to experimental and control conditions using a simple randomization without replacement built into the CATI program (no stratification or minimization given the large proposed sample size in this trial).

### Blinding

Interviewers will be blind to subjects' condition because they will be using the CATI technology. As the first parts of the 8-week and 6-month follow-ups are identical for experimental and control conditions, they will not know the intervention condition to which a subject belongs until questions specific to the use of NRT are asked near the end of the surveys (i.e., after the primary outcome measures are assessed). Further, while it is possible that a participant might 'unblind' themselves to an interviewer by volunteering that they used the nicotine patch, this is still unlikely to have an impact as the interviewers will be part of a separately contracted telephone survey research firm and will not be aware of the hypotheses of this research trial.

### Outcome Measures

#### Primary outcome measures

The primary outcome measure will be 30 day point prevalence of abstinence at 6 months, validated by saliva cotinine samples.

#### Secondary outcome measures

Secondary outcome measures are: (1) 7 day point prevalence of smoking abstinence at 8 weeks post-baseline; (2) reduction in smoking since baseline; (3) compliance with the full 5-week course of nicotine patches provided to experimental condition; (4) challenges with quitting/reducing smoking; and (5) purchase and use of NRT and smoking cessation aids at follow-up periods.

### Data Analysis

#### Power analysis

Quit rates for those who use nicotine patches have been obtained from several sources, including systematic reviews by Fiore et al. [26] and a Cochrane review by Stead and colleagues [16]. Both these reviews indicate a 10% increase in tobacco cessation rates upon using nicotine patches as compared to placebo at 6-month follow-up. This 10% increase is roughly in concordance with the 30 day point prevalence rate for abstinence observed at the 6-month follow-up point of the STOP mass distribution demonstration trial (9%; note that this trial had no control group so the results reflect pre-post changes in smoking rates) [12]. However, we recognize that both of these estimates are probably too large for a pragmatic randomized controlled trial because the impact of interventions is often smaller in real world settings (and pre-post estimates, such as those found in the STOP Study, can also be inflated). Thus, we have chosen to power our trial based on the assumption that our quit rate will be half as large (i.e., a 5% increase in quit rates in the experimental condition versus the control at 6-month follow-up). Finally, we can estimate a 3.7% baseline rate of smoking cessation at 6-month follow-up in a general population sample using findings from the 2008 Canadian Tobacco Use Monitoring Survey (CTUMS) [3]. Given these results, we predict that the subjects in the control condition will display a 3.7% quit rate and subjects in the experimental condition will display a 8.7% quit rate at 6-month follow-up.

Using these assumptions, a power analysis was conducted; this indicated that a total of 403 respondents would be needed per condition to detect a 5% difference at a significance level of .05 with a power of 80% (estimate calculated with continuity correction factored in) [27]. Thus, we have chosen an ideal sample size of approximately 800 respondents in order to conduct appropriate analyses.

Based on our previous research using a similar research design, albeit with problem drinkers rather than smokers [28,29], a 20% attrition between baseline and 6-month follow-up can be expected (the most important follow-up for this study); this would mean that a sample size of 1,000 respondents would be needed at baseline to take part in the randomized trial. Similar follow-up rates have been obtained for smokers in the Ontario Tobacco Survey, indicating that a 20% attrition rate estimate is also reasonable for smokers [30].

From a recent survey of current smokers [10] we know that 62% of 10 or more cigarettes a day smokers say that they would be interested in receiving NRT. Note that the 62% proportion is slightly different from the 58.9% previously reported from this same survey. This is because the proportion reported here for the purposes of generating a sample size estimate was calculated using unweighted data and employs only those smokers from this pilot survey who currently smoke 10 or more cigarettes per day (rather than all smokers who smoked 10 or more cigarettes per day at some point in their life as is employed in the published paper).

Further, from this same survey, we know that 57% of those interested in free NRT say that they would use this NRT to quit, state they would start using it within a week, and would also be willing to have it sent to their homes. Finally, results from this same pilot survey indicate that approximately 14% of those willing to have NRT sent to their homes would screen out due to health contraindications (heart or circulatory problems not including high blood pressure; currently pregnant, intending to become pregnant or breastfeeding) [10]. Note that this estimate of health contraindications is an overly conservative one as the question on heart or circulatory problems asked about lifetime experience. Thus, it is likely that less than 14% of potential subjects will be excluded for this reason. However, we will use the 14% figure in this estimate in order to ensure an adequate sample size.

In conclusion, in order to conduct this trial, we would need to recruit approximately 3,000 respondents at baseline who smoke 10 or more cigarettes per day and who are also willing to take part in an 8-week and a 6-month follow-up with saliva sample collection by mail at each time point (note: saliva samples only collected for the 1,000 participants at baseline who will take part in the randomized trial).

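### On the protocol's own screening rates, 3,000 survey respondents yield about 912 randomised subjects, not the required 1,000; about 3,290 are needed

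*Protocol article*

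**What the plan says.** All the inputs are in the protocol article, under Data Analysis, Power analysis.

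- **Trial size.** The plan is sized "to detect a 5% difference at a significance level of .05 with a power of 80"%, with quit rates of 3.7% (control) and 8.7% (experimental). This gives 403 per condition with a continuity correction, rounded to about 800 in total. Allowing for 20% attrition, "a sample size of 1,000 respondents would be needed at baseline to take part in the randomized trial".
- **Screening step 1.** "62% of 10 or more cigarettes a day smokers say that they would be interested in receiving NRT".
- **Screening step 2.** "57% of those interested in free NRT say that they would use this NRT to quit"; the same 57% also covers starting within a week and accepting delivery at home.
- **Screening step 3.** About 14% of those willing would be excluded for health contraindications. The section regards this as too high, because the pilot question on heart problems covered the whole lifetime. It nevertheless states that "we will use the 14% figure in this estimate in order to ensure an adequate sample size".
- **Conclusion.** "in order to conduct this trial, we would need to recruit approximately 3,000 respondents at baseline who smoke 10 or more cigarettes per day".

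The Methods/Design part of the abstract repeats the pairing: N = 3,000 surveyed and N = 1,000 eligible and randomised.

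**The concern.** The three screening proportions are sequential, and each has a stated denominator, so they multiply. Their product should turn 3,000 respondents into about 1,000 randomised subjects, and it does not. The 3,000 exceeds what is needed only when the last step, the health exclusion, is left out. Yet the text singles out that step as its safeguard for sample size.

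The number of survey interviews is what a team budgets and contracts for, and the section on the experimental condition mentions a limited budget for the patches and the survey. If the survey were closed at the stated number, the trial would be about 9% smaller than required.

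**Working it through.** **1. Reproduce the plan's trial size.** Inputs: p1 = 0.037, p2 = 0.087, d = 0.05, mean rate 0.062, alpha 0.05 (sidedness not stated; two-sided reproduces the plan's figure), power 80%.

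- Uncorrected: n = [1.960 x sqrt(2 x 0.062 x 0.938) + 0.842 x sqrt(0.037 x 0.963 + 0.087 x 0.913)]² / 0.05² = 364 per arm.
- Continuity-corrected: n' = (n/4) x [1 + sqrt(1 + 4/(n d))]² = 403 per arm. This matches the plan.
- Attrition: 800 / 0.8 = 1,000. This matches. (Using 806 gives 1,008, a negligible difference.)

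**2. Recompute the screening yield.**

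- Interested: 3,000 x 0.62 = 1,860
- Willing: 1,860 x 0.57 = 1,060
- Not excluded: 1,060 x 0.86 = 912

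The overall yield is 0.62 x 0.57 x 0.86 = 30.4%. The shortfall is 1,000 - 912 = 88, or 8.8%. The number needed is 1,000 / 0.3039 = 3,290.

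**3. How low must the exclusions be for 3,000 to suffice?** 1 - 1,000/1,060.2 = 5.7%.

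| Exclusion rate | Randomised from 3,000 |
|---|---|
| 0% | 1,060 |
| 5% | 1,007 |
| 10% | 954 |
| 14% (plan) | 912 |

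**4. Power if only 912 were randomised.** After 20% attrition, 912 x 0.8 / 2 = 365 per arm. Inverting the corrected formula gives an effective n = (n' - 1/d)² / n', which goes into the uncorrected power formula.

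- 400 per arm: (400 - 20)² / 400 = 361, power 79.7%.
- 365 per arm (364.7 unrounded): (364.7 - 20)² / 364.7 = 325.8, power 75.5%.

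The result depends on what the quit rates refer to, because the Analysis Plan counts subjects lost to follow-up as smokers and so keeps all randomised subjects in the denominator:

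| Reading, two-sided 0.05 | 1,000 randomised, corrected / uncorrected | 912 randomised, corrected / uncorrected |
|---|---|---|
| Followed-up subjects only, 3.7% v 8.7% | 79.7% / 83.6% | 75.5% / 80.1% |
| All randomised, missing = smoker, rates hold only in those followed up (2.96% v 6.96%) | 79.1% / 83.1% | 74.9% / 79.5% |
| All randomised, 3.7% v 8.7% hold for all | 88.4% / 90.7% | 85.1% / 88.0% |

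The second row uses 0.8 x 3.7% = 2.96% and 0.8 x 8.7% = 6.96%.

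**The case against.** A reader might infer that the trial will not have its stated 80% power. The document does not support that as an unconditional statement, for three reasons.

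- **Power depends on the number randomised, not the number interviewed.** The 1,000 is the stated requirement and recurs in the abstract, the Power analysis and the Analysis Plan. The 3,000 is an estimate of the survey needed to reach it, and nothing in the article makes it a stopping rule or a cap. If recruitment runs to 1,000 randomised, the slip affects only the expected survey workload.
- **The 14% may not hold.** The section itself expects fewer exclusions.
- **The size of any loss depends on the method.** At 365 per arm, power is 80.1% without the continuity correction, and the planned primary test is a logistic regression. If the quit rates apply to everyone randomised, corrected power at 912 is about 85%.

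All three points stand against a flat claim of lost power. They do not rescue the 3,000. The section says that the 14% enters the estimate, the document gives no support for a rate as low as 5.7%, and a gap of about 9% is more than the word approximately can cover.

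A reader might also put the published 58.9% in place of 62% and find a larger shortfall. The section explains why 58.9% is not the planning input: the 62% comes from unweighted data and is restricted to people who currently smoke 10 or more a day. That substitution has no bearing on whether the plan agrees with itself.

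**Conclusion.** The survey size is wrong as written. On the protocol's own rates, 3,000 respondents give about 912 randomised subjects, 8.8% below the 1,000 required, and about 3,290 respondents are needed. The 403 per condition and the 1,000 randomised both reproduce, so the break is confined to the last link in the chain.

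The consequence for power is conditional. It arises only if recruitment stops at 3,000 and the 14% holds. Corrected power would then be about 75.5% rather than 79.7% on the followed-up count, within a range of about 75% to 85% depending on the population to which the quit rates refer. If recruitment continues to 1,000 randomised, power is about 80% as planned.

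These figures assume a two-sided test and assume that the pilot-survey rates carry over to smokers who agree to join the study.

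**What to change.** Make one of two changes, in both the Power analysis section and the abstract.

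- **Keep the target of 1,000.** Restate the baseline survey as about 3,300 respondents (3,300 x 0.3039 = 1,003), and state that recruitment ends when 1,000 have been randomised, not when 3,000 have been interviewed. Cost: a corrected sentence in each place and, if the 14% holds, about 290 to 300 more interviews.
- **If 3,000 is a fixed cap.** Restate the expected trial size as about 912 randomised (about 365 per arm followed up). Give the corresponding power as conditional on the 14% and on the population to which the quit rates refer. Cost: text only.
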